## Abstract

**Background:**

Children’s exposure to toxic stress (e.g., parental depression, violence, poverty) predicts developmental and physical health problems resulting in health care system burden. Supporting parents to develop parenting skills can buffer the effects of toxic stress, leading to healthier outcomes for those children. Parenting interventions that focus on promoting parental reflective function (RF), i.e., parents’ capacity for insight into their child’s and their own thoughts, feelings, and mental states, may understand help reduce societal health inequities stemming from childhood stress exposures. The Attachment and Child Health (ATTACH^TM^) program has been implemented and tested in seven rapid-cycling pilot studies (*n* = 64) and found to significantly improve parents’ RF in the domains of attachment, parenting quality, immune function, and children’s cognitive and motor development. The purpose of the study is to conduct an effectiveness-implementation hybrid (EIH) Type II study of ATTACH^TM^ to assess its impacts in naturalistic, real-world settings delivered by community agencies rather than researchers under more controlled conditions.

**Methods:**

The study is comprised of a quantitative pre/post-test quasi-experimental evaluation of the ATTACH^TM^ program, and a qualitative examination of implementation feasibility using thematic analysis via Normalization Process Theory (NPT). We will work with 100 families and their children (birth to 36-months-old). Study outcomes include: the Parent Child Interaction Teaching Scale to assess parent-child interaction; the Parental Reflective Function and Reflective Function Questionnaires to assess RF; and the Ages and Stages Questionnaire – 3rd edition to examine child development, all administered pre-, post-, and 3-month-delayed post-assessment. Blood samples will be collected pre- and post- assessment to assess immune biomarkers. Further, we will conduct one-on-one interviews with study participants, health and social service providers, and administrators (total *n* = 60) from each collaborating agency, using NPT to explore perceptions and experiences of intervention uptake, the fidelity assessment tool and e-learning training as well as the benefits, barriers, and challenges to ATTACH^TM^ implementation.

**Discussion:**

The proposed study will assess effectiveness and implementation to help understand the delivery of ATTACH^TM^ in community agencies.

**Trial registration:**

Name of registry: https://clinicaltrials.gov/. Registration number: NCT04853888. Date of registration: April 22, 2021.

**Supplementary Information:**

The online version contains supplementary material available at 10.1186/s12887-022-03439-3.

## Administrative information

Note: the numbers in curly brackets in this protocol refer to SPIRIT checklist item numbers. The order of the items has been modified to group similar items (see http://www.equator-network.org/reporting-guidelines/spirit-2013-statement-defining-standard-protocol-items-for-clinical-trials/).

**Table Taba:** 

**Section/item**	**Item No**	**Description**

## Introduction

### Background and rationale {6a and 6b}

Children’s exposure to toxic stress (e.g., parental depression, violence, poverty) predicts developmental problems (e.g., cognitive, motor), behavioural disturbances, physical health problems, and years of life lost to disability, resulting in health care system burden [1–4]. Effective parenting skills can buffer the effect of toxic stress exposure on child developmental and health outcomes [5]. Interventions that focus on supporting effective parenting in the face of parental depression, violence, and other threats to well-being are effective strategies to support healthy child development [6, 7]. Furthermore, parenting interventions that focus on reflective function (RF), that is, parental capacity to understand and thus regulate their own and their child’s thoughts, feelings, and mental states, [8–10], have great potential to improve developmental outcomes of children exposed to toxic stress. Indeed, RF is essential for high quality parent-child relationships and parent-child attachment [11], child development, and health. Specifically, there is evidence for improvement in: cognition [12], communication [13], mental [14], and immune health [15]. Effective early interventions focusing on parental RF, such as the Attachment and Child Health (ATTACH^TM^) [10, 16] program, may help reduce societal health inequities stemming from childhood stress exposures [9, 17].

ATTACH^TM^ is a psychoeducational parenting program delivered in community agencies that serve families with preschool-aged children affected by toxic stress [18]. It was tested in seven rapid-cycling pilot studies with small sample sizes (*n*’s = 10–20 per pilot). Pilots were guided by the IDEAS (Innovate, Develop, Evaluate, Adapt, Scale) Framework^TM^ [18], an innovative clinical trial approach that reduces time from program development to implementation, while ensuring rigour in evaluation [18, 19]. In two phases, we conducted randomized control trial (RCT) and quasi-experimental (QE) pilot studies. In the first, phase, three pilot studies revealed that ATTACH^TM^ significantly improved parent-child relationship quality (*d* = .34–1.5) [9] parents’ RF scores (*d* = .51–2.0) [10], and children’s cognitive and motor development(*d* = .98–2.3; all *p*’s < .05) [9, 10]. These findings led the Harvard Center on the Developing Child to recognize and fund ATTACH^TM^ as a Frontiers of Innovation project (see https://developingchild.harvard.edu/innovation-application/frontiers-of-innovation/), supporting phase two. In the four pilot studies that followed, ATTACH^TM^ significantly improved parent-child interaction quality (*d* = .41–1.5), parental reflective function (*d* = 1.2–1.4), attachment security (eta^2^ = .30–.47), child development (*d* = .47–1.4; all *p*’s < .05) and immune cell gene expression [20, 21]. While these preliminary results are promising, whether ATTACH^TM^ is as effective when delivered by trained agency health and social service providers rather than researchers (as in the first seven pilot studies), in naturalistic community settings remain to be seen.

Further, to our knowledge only two studies of parenting interventions, including our pilot research [20, 22] have shown changes in systemic inflammation in children exposed to toxic stress. Whether ATTACH^TM^ affects novel biomarkers (i.e., immune cell gene expression, DNA methylation) in a larger sample is not known. Addressing this gap offers the rare opportunity to examine how parent-child relationships could buffer impacts of toxic stress on immune cell regulation, via gene expression and epigenetics, which is considered a research priority [23, 24]. Through integrated Knowledge Translation (iKT) and Patient Engagement (PE) approaches [25], where patients,^1^ health and social service providers, and health system administrators are partners [26–28], and along with our funder Canadian Institutes of Health Research (CIHR) Strategy for Patient-Oriented Research (SPOR) collaborators [e.g. Alberta SPOR Support Unit, Saskatchewan Centre for Patient-Oriented Research (SCPOR)], this team proposes to undertake an effectiveness-implementation hybrid (EIH), Type II study [29] of ATTACH^TM^, with co-primary objectives in clinical intervention effectiveness and implementation strategy evaluation [29]. The co-primary objectives evaluate clinical intervention effectiveness and implementation strategy feasibility in naturalistic, real-world, settings, as delivered by community agencies.

### Impact of toxic Stress on parent-child relationships and child development and health

An estimated 25–33% of Canadian and American preschool-aged children are raised in families with at least one toxic stressor [18, 30]. Previous research has found that the developmental costs of exposure to toxic stress are high. Maternal depression is well-known to negatively impact child development [31–33]. Children aged 12 to 24 months exposed to postpartum depression have significantly reduced cognitive development characterized by lower communication scores [34] and 2 to 6 year olds have reduced cognitive (e.g., communication, problem-solving, personal, social) and motor development [35]. Six to 18 month-old children exposed to family violence are at greater risk for developmental problems [23, 24] and specifically lower cognitive and motor domain scores [36]. One to 3 year-old children exposed to family violence also experience cognitive and motor delays, specifically reduced problem-solving and fine motor skills respectively [37]. Similar impacts of poverty on children’s developmental attainment have also been observed [38, 39]. Toxic stress also affects physical health and the immune system, as associated with higher systemic inflammation in adulthood [40–42] and inflammatory disease risk (e.g. cardio-metabolic disease, cancer, asthma, depression) [43, 44]. Recently, inflammation has been proposed as the intermediary between toxic stress exposure and children’s cognitive and mental developmental outcomes [45, 46].

A troubling additional consequence of toxic stress exposure is compromised parent-child relationships, characterized by reduced parental sensitivity/responsiveness and insecure parent-child attachment [47, 48]. A systematic review [49] revealed that reduced parental sensitivity/responsiveness undermines children’s attachment security, development, and health, especially in cognitive and motor domains. Findings held across a diverse range of cultures [49], including Canadian Indigenous peoples [50]. The review concluded that less sensitive/responsive parental behaviors and cognitions are consistent with the toxic stressor of addiction (e.g., due to addiction-related inconsistency in infant care, changing mood) [51] or depression (e.g., due to symptoms of fatigue, reduced concentration) [32] that induce parents to miss and thus fail to respond to their children’s cues [52, 53]. In general, children’s development is negatively impacted when parents fail to: (1) recognize and respond to children’s cues that signal needs and (2) regulate their children’s mental and emotional states [48]. Both are targets of the ATTACH^TM^ intervention.

Toxic stress also undermines children’s attachment security, which develops in infancy from the emerging expectation that the infant’s basic needs for soothing, comfort, and protection from danger will be met (or not) by their parent [54–57]. Insecure attachment predicts a well-studied host of developmental problems [12, 49–54], including cognitive challenges [58, 59], and an emerging literature on physical health problems linked to inflammation [15, 60]. High quality parent-child relationships, characterized by secure attachment at 12 months of age, predicted reduced risk for inflammatory disease *30 years later* [15]. Further, research from our team found that high quality maternal-child relationships characterized by sensitivity/responsiveness buffered the effect of toxic stress on child immune system activity [61]. Reduced parent-child relationship quality thus appears to leave a long-lasting imprint on children’s development and health.

### Parent-child relationships and parental reflective function (RF)

High quality parent-child relationships, characterized by sensitivity/responsiveness to children’s states and emotions, are in part the result of parental RF [62], Parental RF is necessary to perceive and respond to a child’s cues for comfort, soothing, or exploration [63–65], and is characteristic of optimal parent-child relationships. For example, a parent who is unable to recognize their child’s fear of separation is likely to fail both to reassure the child that they will return and to regulate their child’s stress response. Parents’ experiences of depression, violence, and/or addictions) [66–68] and past traumas (e.g. histories of unresolved grief, emotional, physical, or sexual abuse) [69, 70] predict parents’ negative and distorted representations of reality and frightened, frightening, or dissociated behaviors during interactions with their young children [66–70]. These parents are at risk for reduced RF, adverse parent-child relationship quality and their children are at risk for insecure attachment and long-lasting negative development and health outcomes [5, 18]. These parents are the target of the ATTACH^TM^ intervention.

### Parental RF focused interventions

Three meta-analyses reveal that high parental RF can buffer the negative effects of toxic stress [11, 71, 72]. Our meta-analysis demonstrated that RF is modifiable by intervention, and that RF-focused parenting interventions predict improvements in parent-child relationship quality in families affected by a variety of toxic stressors [11]. Preserving optimal RF when experiencing toxic stress allows parents to attribute affective states to their children and respond to meet their children’s needs, thus promoting healthy parent-child relationships [63, 65, 73]. Targeting parental RF improvement is thus a promising way to tackle the impacts of toxic stress on vulnerable children’s development. With respect to immune health, emerging evidence suggests that parenting interventions can reduce systemic inflammation [22] and pro-inflammatory immune cell epigenetic programing [74] in children 10 years after intervention. Whether RF-focused interventions like ATTACH^TM^ affects children’s inflammation is unknown.

### ATTACH^TM^ pilot studies using innovative clinical trial and iKT approaches

The focus of ATTACH^TM^ on RF as well as the design of key intervention components were determined in collaboration with knowledge users including community health and social service agency administrators and health and social service providers. First, they pointed out that the most effective parenting programs tend to include a focus on RF [11, 75], and that these programs are few in number, thus RF became the target of ATTACH^TM^. Second, collaborators noted that existing RF-focused parenting programs typically involve months or years of psychotherapy provided by expensive clinical psychologists or psychiatrists [76], rendering these approaches cost-prohibitive and thus unrealistic in community settings. ATTACH^TM^ was thus designed to be a shorter intervention and simple enough to be administered by professionals with an undergraduate education in a health-related field, typical of partner agency staff. Third, many parenting programs tend to be designed for a narrow patient population (e.g., those affected by maternal addiction or depression, but not both) [77], making such programs difficult to administer in agencies serving more complex clients. Thus, ATTACH^TM^ was designed to help complex patients by targeting rapid learning of parental RF skills via practice, from which many could benefit. Finally, parenting programs often do not incorporate co-parents, defined as individuals who are a main source of parenting support (e.g., other parent, partners, grandparents, friends) [78, 79]. As a result, the inclusion of co-parents in ATTACH^TM^, was guided by health and social service providers /knowledge users’ suggestion [80].

Since completion of the seven pilot studies, we made additional changes, based on feedback from collaborators. First, we were advised to address the broad range of family structures served in partners’ agencies including both sexes/self-reported genders of parents. While mothers and children were the focus in pilots, ATTACH^TM^ has now been adapted to the primary child caregiver (hereafter referred to as “parent”, whether mother, father, grandparent, foster carer, cis-or trans-gender, etc.) and their source of co-parenting support. As a result, ATTACH^TM^ will be more applicable across a diversity of family units and more realistic for implementation in community agencies. Second, we were advised by health and social service providers /knowledge users to make the ATTACH^TM^ materials more ethnically diverse. We have since changed the manual images to reflect a variety of cultures and names. Finally, we were advised by agency health and social service providers to make the training more accessible. To respond to this suggestion, we developed an on-line platform for training and accrediting health and social service providers to deliver ATTACH^TM^ independently in their agencies (beta version at https://attach.teachable.com) and resulted in trademarking the ATTACH^TM^ name. In summary, our innovative clinical trial and iKT approaches resulted in targeting the ATTACH^TM^ intervention design to address key agency needs including cost-effective programming (shorter duration) that is aligned with staff education level, broadening the focus to include a variety of at-risk parents and their co-parents, and now to include parents and co-parents of any description. We also responded to suggestions to make materials more ethnically diverse, and to develop an on-line training platform. While our iKT approaches involved many collaborators, we did not systematically engage with parents in intervention design. We anticipate the benefits of more systematic and sustained parent “patient” (see footnote 1) engagement along with iKT approaches in our proposed project.

### Objectives {7}

Building on input from community health and social service agency administrators and health and social service providers, our completed pilot work, and the urgent need for RF interventions to address impacts of toxic stress on vulnerable children in the community, this team aims to address two co-primary objectives, Thus, our EIH design (Type II) [29] addresses co-primary objectives in Effectiveness of Clinical Intervention (Objective 1) and Feasibility of Implementation Strategy (Objective 2). We will complete this work with the assistance of our Community Engagement Committee (CEC), Patient Engagement Committee (PEC) and Support for Patient Oriented Research (SPOR) Committee.

#### Objective 1 (quantitative arm)

With quasi-experimental methods we will (1a) Evaluate ATTACH^TM^ impacts on parent-child relationship quality (primary outcome), parental reflective function, and child development; (1b) determine whether ATTACH^TM^ is equally effective across patient populations (and for whom it works best/worst); (1c) evaluate whether ATTACH^TM^ impacts immune biomarkers indicative of inflammatory disease risk, i.e. gene expression and DNA methylation; and (1d) evaluate the long-term impact of ATTACH^TM^ (3 months post-intervention).

#### Objective 2 (qualitative arm)

We will (2a) Evaluate implementation benefits, facilitators, barriers, and challenges from patients’, health and social service providers’, and health system administrators’ perspectives; and (2b) evaluate the utility of our new ATTACH^TM^ e-learning platform.

### Trial design {8}

This EIH type 2 [29] study is a quasi- experimental evaluation of the ATTACH^TM^ program and implementation feasibility [75, 76]. **Objective 1: ATTACH**^**TM**^
**Impacts**, will be addressed via a quasi-experimental design to closely approximate service delivery models in agencies that do not typically employ control groups. Moreover, a RCT design, even employing wait-list controls was deemed unacceptable and even unethical by parents, health and social service providers, and health system administrators in engagement activities surrounding the preparation of this proposal. **Objective 2: ATTACH**^**TM**^
**Implementation Feasibility,** will be addressed via Normalization Process Theory (NPT) to understand factors that promote or inhibit interventions from being embedded in practice [75–77]. Developed in response to recognition of the large gap between intervention development and intervention use in health care—the ‘know-do gap’—, NPT is intended to uncover factors that interfere with the routine or “normal” incorporation of interventions into health care [78]. NPT will guide qualitative semi-structured interviews and analysis exploring patients’, health and social service providers’, and health system administrators’ perceptions and experiences of the benefits, facilitators, barriers, and challenges to ATTACH^TM^ implementation in community agencies.

## Methods: participants, interventions, and outcomes

### Participants

#### Objective 1

##### Parents, co-parents, and children

Those participating families (both mother and mother-identified co-parenting support person) participating in services or programs in the partner agencies are our study population.

#### Objective 2

Parents, Co-Parents, as well as their health and social service providers. Those who have completed the ATTACH^TM^ program or have been responsible for its delivery in partner agencies.

##### Stakeholder engagement

Building on our successful iKT efforts in our pilot work, we will systematically build stakeholder engagement into our study design. Key stakeholders including the Parent Engagement Committee (PEC), the Strategy for Patient Oriented Research (SPOR) Committee, and the Community Engagement Committee (CEC) will be involved in the proposed research. The PEC is defined as a team of individuals who are involved in co-building the intervention, with parents invited to partner and provide feedback on intervention implementation and evaluation. Parents are defined broadly, inclusive of individuals with personal experience of an issue; who provide care or support to those affected by an issue; and with indirect experience of an issue, through family or friend experience or professional practice. The SPOR Committee is defined as a team of individuals who will guide and help oversee the research on the use of patient (parent) and other stakeholder engagement and integrated knowledge translation activities. Also, the CEC is defined as a team of health and social service providers, and administrators in agencies who will have the chance to participate in the project roll-out, participate in interviews as participants, learn about implementation barriers and facilitators, and have opportunities to take part in ATTACH^TM^ training and ultimately independent delivery and evaluation.

### Study setting {9}

#### Objective 1

Settings include our partner agencies in Alberta, Manitoba, and Saskatchewan that serve families experiencing toxic stress We will work with 100 new families from an initial 4 community agencies (Calgary Urban Project Society, Calgary, AB, Discovery House Women’s Shelter, Calgary, AB, Sonshine Community Centre, Calgary AB, and Steinbach Family Resource Centre, Steinbach, MB) and additional community partners (Elizabeth House, Calgary, AB, Regina Transition House, Regina, SK, Marymound, Winnipeg, MB, SOFIA House, Regina, SK, Elizabeth Fry Society, Ottawa, ON) are dissemination targets. The initial 4 implementation sites have a successful history of delivering programs focused on promoting health and development of children in families affected by toxic stress and provide an optimal testing ground for the ATTACH^TM^ intervention. Currently, these agencies do not offer any RF-based parenting programs. The ATTACH^TM^ program will be added on to their existing services or programs. and will disseminate knowledge to additional partners over the course of the study. **Objective #2:** For the qualitative component of the study, we will interview study participants who complete the ATTACH^TM^ intervention in the initial 4 community agencies (Calgary Urban Project Society, Calgary, AB, Discovery House Women’s Shelter, Calgary, AB, Sonshine Community Centre, Calgary AB, and Steinbach Family Resource Centre, Steinbach, MB), as well as their health and social service providers and agency administrators at the same partner agencies, using NPT [75, 76, 79] .

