#### Objective #2

Participants (i.e., parents, co-parents, community health and social service agency administrators and health and social service providers) must be adults (18 years of age or older), and English speaking and reading, and knowledgeable or experienced in parenting programs.

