##### Delayed post-assessment

Three months after the post-assessment data collection is complete, parents will again be asked to evaluate the ongoing effectiveness of ATTACH provide observational, and questionnaire to evaluate the ongoing effectiveness of ATTACH^TM^.

#### Objective 2

NPT interviews will begin as soon as the first family completes the ATTACH^TM^ Reflective Function Intervention Phase and will continue until data saturation is attained, i.e., the degree to which new data repeats or is redundant with what was expressed in previous data [92]. We will employ a stopping rule: Data collection in a category (patient, health and social service providers, and health care administrator) will cease when three interviews in a row offer less than 5% new information (i.e., only one new code to one question of 19 in interview guide offers new information).

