##### Quantitative component

We will recruit until we have completed all study components with 100 new families, a sufficient *n* to detect minimum *d* = .34 for pre- /post- assessment differences in parent-child relationship quality. From discussions with agency health and social service providers and administrators, it will be feasible to recruit 30 families (including parents, co-parents, and children) from each agency, from patients currently seeking service, to retain 20 of them for 3 months postintervention for follow-up (any longer was deemed unrealistic given potential for patient relocation). Specifically, iKT and end-of-grant dissemination will be planned in partnership with agency health and social service providers and administrators.

#### Objective 2

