##### ATTACH^TM^ implementation feasibility

Patients, health and social service providers and administrators from each of the five initial agencies will be recruited via convenience sampling methods. We anticipate 4 patients, 4 health and social service providers, and 4 decision makers will be recruited for interviews from each agency, for a total of 20 participants in each category.

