#### Objective 2: ATTACH^TM^ implementation feasibility

Analysis will occur in two parts. First, interviews will be transcribed and coded and examined for key learnings that may offer guidance to implementation in agencies. These learnings will be shared with the Executive Team, PEC, and CEC and discussed so that appropriate adjustments may be made to facilitate ATTACH^TM^ normalization in agencies. Second, all transcripts will be coded using the stages of thematic analysis including familiarization, coding, theme development, and data reporting [100]. Theme and sub-theme development will be deductive, using a priori codes dictated by interview questions to explain factors that promote or inhibit interventions from being embedded in agency practice. Two trainees will code the data, supervised by [name], who is experienced in qualitative data analysis. Data will be managed with QSR International Nvivo12 [101]. Once themes and sub-themes are finalized, findings summarized in a draft report and shared with key informants as a validation check [101].

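### Parent interviews are open only to families who complete the programme, so first-hand evidence on barriers is survivor-biased; separately, the saturation threshold (below 5%) disagrees with its own definition (1 of 19 questions, 5.26%).

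*Protocol article*

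**What the plan says.** **Who is interviewed.** Under Study setting {9}, Objective 2, the protocol article says "we will interview study participants who complete the" ATTACH intervention in the four initial agencies, "as well as their health and social service providers and agency administrators at the same partner agencies". The Participants section for Objective 2 describes the group as "Those who have completed the ATTACH^TM^ program or have been responsible for its delivery in partner agencies". The Objective 2 eligibility text does not mention completion; it asks for adults, "and English speaking and reading, and knowledgeable or experienced in parenting programs". Under Recruitment {15}, interviewees "will be recruited via convenience sampling methods". The participant timeline starts interviewing once the first family has finished the intervention phase.

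**What the interviews are for.** Objective 2 is co-primary. Part 2a covers benefits, facilitators, barriers and challenges as seen by three groups: patients (parents), providers and administrators.

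**Expected loss.** Sample size {14} expects 30 families recruited per agency, "to retain 20 of them for 3 months postintervention for follow-up". Recruitment {15} gives the totals as up to 150 treated, 100 retained, from five agencies.

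**When interviewing stops.** Under Participant timeline {13}, Objective 2, data collection in a category "will cease when three interviews in a row offer less than 5% new information (i.e., only one new code to one question of 19" in the interview guide. The planned size is 4 interviews per category per agency, 20 per category and 60 in all.

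**The concern.** There are two separate points.

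The first is selection. A parent who left because sessions were impractical, unwelcome or unhelpful is the most direct source on barriers from the patient side, and that parent is not eligible for interview. Parents who stayed can describe only barriers they overcame. The interview learnings are also to be fed back during the study so that delivery can be adjusted (Statistical methods, Objective 2), so the selected view can shape the programme as well as the report on it.

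The second is the stopping rule. Its threshold and the explanation of that threshold give different answers for the same interview. Two analysts following the text could close a category at different points.

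**Working it through.** **1. Is there any route in for early leavers?** Setting the sections side by side:

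- Study setting {9}: parents who complete.
- Participants, Objective 2: completers, or those who delivered the programme.
- Timeline {13}: interviews begin when the first family completes.
- Eligibility {10}, Objective 2, and Recruitment {15}: completion is neither required nor waived.
- Ethics section: data from those who withdraw are kept for attrition analyses unless removal is requested, but no interview about reasons is planned.

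Two sections impose the limit and none lifts it.

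**2. How many families could this exclude?** The planned loss first:

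- Per agency: 1 − 20/30 = 33.3%.
- Overall: 1 − 100/150 = 33.3%, that is 150 − 100 = 50 families.

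The two statements agree. The retention point is 3 months after the intervention, so the 50 mix families who stop during the programme with completers who miss follow-up. The latter remain eligible for interview. The split is not given, so I take a share *f* of the loss as occurring after completion and compute the excluded number as 50 × (1 − *f*):

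| *f* (assumed) | Excluded | Share of 150 |
|---|---|---|
| 0 | 50 | 33.3% |
| 0.5 | 25 | 16.7% |
| 1 | 0 | 0% |

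**3. Does the stopping rule agree with itself?**

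- Threshold: new information below 0.05.
- Explanation: one question of 19, 1/19 = 0.0526, which is not below 0.05.
- With 19 questions, the threshold therefore allows 0 questions with new information, while the explanation allows 1.
- One question falls below 5% only if the guide has at least 21 questions (1/20 = 5.0% exactly; 1/21 = 4.8%).

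Any run of three interviews that meets the zero version also meets the one-question version, so the second can only stop at the same interview or sooner.

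**4. How early could a category close?** Saturation is defined against what earlier interviews said, so the first interview cannot count towards the run. The formal minimum is interviews 2, 3 and 4, hence 4 interviews. That equals one agency's planned share of a category. The rule runs by category, with no requirement that every agency has contributed.

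**5. What is the planned number of interviews?** Study setting {9} names 4 initial agencies; Recruitment {15} uses 5.

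- 4 agencies: 4 × 4 = 16 per category, 48 in all.
- 5 agencies: 4 × 5 = 20 per category, 60 in all.

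The stated 20 and 60 need five agencies.

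**The case against.** The strongest reply is that barriers are not sought from parents alone. Providers and administrators make up 40 of the 60 planned interviews, Objective 2a names their perspectives too, and providers who deliver sessions will often know why a family left. The theory guiding the interviews also concerns embedding the programme in agency practice more than individual reasons for leaving. This stands in part. A reader might infer that the reasons for dropout will be missed altogether, or that feasibility is bound to look better than it is; the documents support neither. What is lost is the early leavers' own account, which matters because the objective lists the parent perspective separately.

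A reader might also infer that all 50 lost families are shut out. The retention point is after the intervention, so 50 is only the upper end.

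On the stopping rule, it is fair to say that the gap is 0.26 percentage points and looks like rounding, and that the bracketed text supplies a usable version. The practical difference is still none against one question. Pooling the three interviews does not rescue the wording: one of 3 × 19 = 57 is 1.75%, but two of 57 (3.51%) would then pass as well, against the bracketed limit of one.

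Three further inferences should be resisted:

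- The stopping rule does not cause the exclusion of early leavers. It governs when interviewing ends, not who is eligible.
- Three interviews cannot close a category, for the reason in step 4 of the working. Four is the formal minimum, and it is an extreme case.
- Counting new codes does not conflict with the analysis plan. It says "Theme and sub-theme development will be deductive, using a priori codes dictated by interview questions", but it does not say that only such codes are used, and a predefined code that first appears in a later interview can count as new.

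**Conclusion.** The point holds in two limited parts. First, parent interviews are restricted to completers by explicit text in two sections, so first-hand parent evidence under a co-primary objective is survivor-biased. Between 0 and 50 of 150 families are affected; the figure depends on how much of the planned loss happens during the programme, which the protocol does not state. The direction and size of any effect on the feasibility conclusions cannot be derived from the document. Second, the stopping rule contradicts its own definition (below 5% against 5.26%). This is a small numerical slip, but it changes the permitted number of questions with new information from 0 to 1.

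The study can run as it is. Both parts should be corrected because the cost is low and recruitment was already in progress when the protocol was published.

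**What to change.** 1. Amend Participants (Objective 2) and Study setting {9} so that parents who started the programme and stopped early are eligible for interview. Reserve some of the already planned parent interviews for them, for example one per agency where such a parent can be reached. That number is a suggestion and is not derived from the document. If eligibility is not widened, state the restriction as a limitation of the parent evidence.
2. Restate the stopping rule once: a category closes when at most 1 of the 19 questions yields a new code in each of three consecutive interviews. Apply it only after every participating agency has contributed interviews in that category.
3. Reconcile the number of agencies between Study setting {9} (4) and Recruitment {15} (5), then fix the interview count at 16 or 20 per category accordingly.

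The cost is an amendment to the protocol and consent wording, extra effort to reach families who have left, and possibly a few more interviews in categories that would otherwise close early. Reserving planned slots adds no parent interviews to the total.
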